### 10.2 Planned recruitment rate

The recruitment period is 36 months. The recruitment projection is shown below (figure 4). The pause in recruitment has impacted on recruitment. The figure below will be updated (at the next protocol amendment) once we have re-established recruitment.

Figure 4: recruitment projection

[figure not shown]

### 10.3 Statistical analysis plan

Statistical analyses will be according to the intention to treat principle with a per protocol analysis performed as a sensitivity. The per protocol analysis will exclude participants who were not compliant (at less than 70%) with their study medication. All analyses will be governed by this comprehensive SAP which will be agreed by the Trial Steering Committee (TSC) and approved by the independent Data Monitoring Committee (DMC) prior to any analyses being undertaken. Unless pre-specified, a 5% two-sided significance level will be used to denote statistical significance throughout. There will be no interim analyses undertaken. In line with other recent COPD trials it is not envisaged that the DMC will be monitoring the study in order to terminate it prematurely on finding evidence of overwhelming benefit – nor will they terminate it for futility.

The primary outcome - number of COPD exacerbations requiring antibiotics and/or oral corticosteroids in the 12 months after randomisation - will be compared between randomised groups using negative binomial regression with length of time in the study as an offset. Estimates will then be adjusted for centre and other baseline covariates that are known to be strongly related to outcome (e.g. age, smoking, COPD hospitalisations in year prior to study – these will be pre-specified in the SAP). Despite the patients being followed-up for a single year, some will withdraw early and, given their chronic illness, some will inevitably die. Use of an overdispersion parameter should improve the model estimates as it takes between patient variability in exacerbation rate into account. The negative binomial model assumes that each patient has their own underlying exacerbation rate which follows a Poisson distribution, but the expected rate is allowed to vary across patients according to a gamma distribution. The shape parameter from the gamma distribution explicitly represents the variability between patients. The negative binomial model coincides with the Poisson model when this dispersion parameter is zero. Assumptions of this model are that exacerbation counts are assumed to vary about means that differ for each patient, with means varying across the population. Hence, the negative binomial model more effectively accounts for increased exacerbation events amongst patients withdrawing early.

To further assess the impact of death (estimated at around 6% of the randomised subjects in the first 12 months after randomisation) on our potential treatment effect, a sensitivity analysis will be undertaken by excluding those subjects who have died. If there is any indication of a differential effect on deaths by treatment, models may be considered that allow the censoring to be informative. For participants that are lost to follow up at some time during the 12 month follow-up (estimated to be around 15% of those randomised), their information will be included in the statistical models up to the point that they are lost to follow up. Sensitivity analyses will be undertaken using multiple imputation (assuming data are missing at random), and, if necessary, and the data permit, specify the mechanism of missing data via a pattern mixture model assuming informative missingness.

The secondary outcomes - total number of COPD exacerbations requiring hospital admission and total number of emergency hospital admissions (all causes) - will each be analysed in the same way as for the primary outcome described above.

Disease related health status (measured using the COPD Assessment Test (CAT)), generic health-related quality of life (EQ5D-5L) and Hull Airways Reflux Questionnaire (HARQ), FEV1 and FVC are each measured at baseline, and at 6 and 12 month follow-up. A mixed effects model will be used to compare each outcome by randomisation group unadjusted and adjusted for centre, patient characteristics and/or baseline clinical variables. Mixed effects models assess rates of change with allowance for the correlation structure of the repeated measures data. Fixed effects will include assessment, treatment, centre and other relevant patient related variables and patient will be fitted as a random effect. A treatment-time interaction will be included to assess the differential treatment effect on rate of change in outcome. Alternative correlation structures will be considered and the most appropriate selected based on the log-likelihood and Akaike's Information Criterion (AIC) of the model. All randomised patients with at least one valid measurement will be included in the analysis and missing outcome data assumed to be missing at random.

As sensitivity analyses, (a) the mixed effects models will be repeated on those patients who survive the 12 month follow-up only (b) where appropriate to do so a pre-specified value will be imputed for those patients who died during follow-up (e.g. zero value for EQ-5D-5L) (c) multiple imputation will be undertaken assuming data are missing at random (d) if missing data are thought to be informative, then consideration will be given to the use of appropriate models such as the pattern mixture model.

Descriptive statistics for health care utilisation and the occurrence of adverse events will be produced and, if appropriate, a comparison will be made between randomised groups using the chi-squared test, t-test etc. Poisson regression may be used to compare multiple events of the same type between randomisation groups. All-cause mortality rate and time to first COPD exacerbation, will be compared between randomised group using a log-rank test and Kaplan-Meier survival curves. Adjustment for potential covariates will be undertaken using Cox proportional hazards regression.

Compliance will be assessed by pill counting of the returned containers at each of the follow up visits and the proportion of compliant patients compared between randomisation groups using the chi-squared test. Major adverse cardiovascular events (MACE) in randomisation groups will be compared using the chi-squared test.

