## **7.3 Randomisation**

A computerised randomisation system created by CHaRT will allocate participants with equal probability to intervention or control arms, stratified by centre (secondary care site, primary care area), and where participants were identified (primary care, secondary care). This randomisation application will be available 24 hours a day, 7 days a week as an interactive internet based application. Randomisation should only be carried

out once the eligibility has been confirmed by a medical doctor listed on the delegation log, and following consent. The randomisation application will be available to people listed on the delegation log with that responsibility and is not restricted to those who confirm eligibility or take consent.

Participants will be randomised to bisoprolol or placebo. Bisoprolol will be in the form of 1.25mg tablets. Each bottle will contain 168 tablets. The first bottle of study medication (or placebo) will be provided to the participant via the Central Clinical Trials Pharmacy. This first bottle of study medication will be delivered to participants via a courier service (or other signed for delivery service) operated by a third party.

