## 10 STATISTICS AND DATA ANALYSIS

### 10.1 Sample size calculation

The multicentre Evaluation of COPD Longitudinally to Identify Predictive Surrogate Endpoints (ECLIPSE) study reported the frequency of COPD exacerbation in 2138 patients [57]. For patients identical to our target population ( $\geq 2$  self reported COPD exacerbations in a year requiring antibiotics and/or OCSs), the mean (SD) number of COPD exacerbations within the subsequent one year was 2.22 (1.86), ([name], ECLIPSE statistician, personal communication). The Cardiac Insufficiency Bisoprolol Study II (CIBIS -II) reported that the proportion of participants who stop taking study medication in a trial of bisoprolol vs placebo to be about 15% and this is comparable with what has happened in TWICS [38].

Assuming a similar rate in the placebo arm 669 participants are needed in each arm of the trial to detect a clinically important reduction in COPD exacerbations of 15% (i.e. from an average of 2.22 to 1.89) with 90% power at the two-sided 5% significance level. Allowing for an estimated 15% withdrawal from study treatment the aim will therefore be to recruit 787 participants per arm (i.e. 1,574 in total).

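### Poisson regression is offered for repeated adverse-event and health-care-use counts with no allowance for overdispersion or follow-up time, so p-values could be too small

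*Protocol*

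**What the plan says.** Protocol section 10.3 deals with event counts in three places.

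- **Exacerbations (primary outcome).** Negative binomial regression with time in the study as an offset. The reason given is variation between patients: "Use of an overdispersion parameter should improve the model estimates as it takes between patient variability in exacerbation rate into account". The section adds that this model reduces to the Poisson model only when the dispersion is zero.
- **COPD admissions and all-cause emergency admissions.** Analysed in the same way as the primary outcome.
- **Health care utilisation and adverse events.** Descriptive statistics first and, if appropriate, simple group comparisons, with the chi-squared test and t-test given as examples. Then: "Poisson regression may be used to compare multiple events of the same type between randomisation groups". Nothing is said here about dispersion, the variance estimator or length of follow-up.

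For significance, the section states that, unless otherwise pre-specified, "a 5% two-sided significance level will be used to denote statistical significance throughout". Use of primary or secondary care for respiratory events is a secondary outcome in section 3.4, counted per year of treatment.

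**The concern.** Poisson regression with model-based standard errors takes the variance of a patient's count to be equal to its mean. If some patients are prone to many events and others to few, the variance exceeds the mean, the standard errors are too small, and the test rejects a true null hypothesis more often than its nominal level. Section 10.3 makes this argument for exacerbations, then names Poisson without qualification for the remaining repeated events and gives no reason for the change.

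Respiratory health care contacts are the clearest case. Many will arise from exacerbations, so if exacerbation rates differ between patients, contact rates very probably do too. The section already extends negative binomial to all-cause emergency admissions, which are not only exacerbations.

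Follow-up time is a second gap. Section 10.3 expects about 15% of participants to be lost to follow-up and about 6% to die within the year. Under section 9.2 the recording period for serious adverse events and adverse reactions also differs between those who complete treatment, those who stop early and those who never start. Counts compared without an offset ignore these differences.

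At stake are spurious signals of benefit or harm in secondary and safety comparisons.

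**Working it through.** **Inputs from the protocol**

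- Mean and SD, section 10.1: "the mean (SD) number of COPD exacerbations within the subsequent one year was 2.22 (1.86"), so the SD is 1.86.
- Assumed effect, section 10.1: 2.22 to 1.89, a difference of 0.33.
- Two-sided 5% level and 90% power, sections 10.1 and 10.3.
- Allocation, section 7.3: the system will "allocate participants with equal probability to intervention or control arms".
- Withdrawal, section 10.1: "Allowing for an estimated 15% withdrawal from study treatment the aim will therefore be to recruit 787 participants per arm".

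**The plan's own figure**

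n per arm = 2 × (1.96 + 1.2816)² × 1.86² / 0.33² = 668 after rounding up. The t-test version gives 668.6, hence 669 as stated. Then 669 / 0.85 = 787.06, stated as 787. The sample size reproduces, so the SD of 1.86 is the one the trial was planned on.

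**Overdispersion in the exacerbation figures**

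- Variance = 1.86² = 3.4596.
- Variance/mean = 3.4596 / 2.22 = 1.558. A Poisson count would give 1.
- Negative binomial dispersion k, from variance/mean = 1 + k × mean: k = 0.558 / 2.22 = 0.25.
- Unscaled Poisson standard errors are too small by a factor of √1.558 = 1.25.
- True two-sided error = 2 × [1 − Φ(1.96 / 1.25)] = 11.6%.

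A simulation of negative binomial counts under the null (787 per arm, Poisson Wald test, 40,000 runs) gave 11.5%.

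**Other events**

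The protocol gives neither a mean nor a dispersion for adverse events or utilisation, so every mean and dispersion below is an assumption, except that 0.25 is the value implied by the exacerbation figures. The ratio 1.558 should not be carried over unchanged, because under a negative binomial model it changes with the mean. True error of a nominal 5% unscaled Poisson test, with variance/mean = 1 + k × mean:

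| Dispersion k | Mean 0.1 per year | Mean 0.3 | Mean 1 | Mean 5 |
|---|---|---|---|---|
| 0.25 | 5.3% | 5.9% | 8.0% | 19.2% |
| 1 | 6.2% | 8.6% | 16.6% | 42.4% |
| 2 | 7.4% | 12.1% | 25.8% | 55.5% |

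Simulation checks: 5.7% (mean 0.3, k 0.25), 11.7% (mean 0.3, k 2) and 19.1% (mean 5, k 0.25). Inflation is slight for rare events with modest dispersion, and large for frequent events such as health care contacts.

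**The case against.** The case against has several parts, and most of it stands as a limit on the point.

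- **The plan does not contradict itself.** A reader might infer that it calls these counts overdispersed and then ignores this. It does not: its remarks on dispersion concern exacerbations. Extending them to adverse events and utilisation is an inference, a strong one for respiratory health care use and weaker for adverse events. Section 9.2 excludes exacerbations, and admissions caused by them, from adverse events and serious adverse events.
- **Poisson is not the only method named.** The chi-squared test and t-test come first. A t-test on per-patient counts estimates its variance from the data, and a chi-squared test on patients with or without an event does not assume Poisson variation. Poisson is, however, the only regression model named for these counts.
- **The wording is permissive, and the SAP is not shown.** The protocol says that Poisson may be used and specifies no variance estimator. Section 10.3 places all analyses under a comprehensive SAP, where a scale factor or robust errors could be set. So one cannot say that the p-values will be too small, only that they could be. This does not dispose of the point: the protocol is not silent but names a model, without the allowance it makes for its other counts.
- **The main outcomes are protected.** Exacerbations and both admission counts have negative binomial regression, MACE has a chi-squared test (section 10.3), and the within-trial economic analysis uses bootstrapping (section 10.5).

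**Conclusion.** The point holds as a minor one, limited to optional secondary and safety comparisons of repeated adverse events and health care utilisation. If Poisson regression is used there with unscaled standard errors, and event rates vary between patients, the true error exceeds 5%.

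It would be tempting to quote 11.6% as the error for these analyses. The documents do not support that: the figure belongs to counts with the mean and variance of exacerbations and serves only as a reference. With the same dispersion, inflation is under one percentage point for events at 0.1 to 0.3 per year and reaches 8% to 19% at 1 to 5 per year. Higher dispersion would make it worse, but the protocol gives no value for these events. The calculation assumes negative binomial counts, equal follow-up and the same dispersion in both arms under the null.

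That the sentence makes no allowance for dispersion or follow-up time is plain from the text. How much this would matter in practice is uncertain.

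**What to change.** In section 10.3, replace the Poisson sentence with: *Repeated events of the same type will be compared using negative binomial regression, or Poisson regression with robust or scaled standard errors, with log follow-up time as an offset.* Follow-up time should be the period over which that type of event was recorded for the participant, given the differing periods in section 9.2.

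Either model is acceptable as a first choice; the SAP should state which before any analysis. The cost is one sentence, with the same data and software. Little is lost if the counts prove not to be overdispersed, since section 10.3 itself notes that the two models then coincide.

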### **3.2 Secondary objectives**

The secondary objectives are to compare the following outcomes between participants treated with bisoprolol, and those treated with placebo:

- Hospital admissions with a primary diagnosis of COPD exacerbation.
- Total number of emergency hospital admissions.
- Total number of major adverse cardiovascular events (MACE).
- Lung function (during the COVID-19 pandemic, lung function cannot be assessed in participants).
- Changes in breathlessness during treatment.
- All-cause, respiratory and cardiac mortality.
- Drug reactions and serious adverse events.
- Health related quality of life.
- Disease specific health status.
- Health care utilisation.
- Incremental cost-per-exacerbation avoided.
- Costs to the NHS and patients and lifetime cost-effectiveness based on extrapolation modelling.
- Modelled lifetime incremental cost per Quality Adjusted Life Year.
- Treatment effects in participants with and without clinically diagnosed heart disease.

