### 3.4 Secondary endpoints/outcomes

- Total number of COPD exacerbations requiring hospital admission\*.
- Time to first exacerbation of COPD.
- Total number of emergency hospital admissions (all causes)\*.
- Total number of major adverse cardiovascular events (MACE) (defined by cardiovascular death, hospitalisation for myocardial infarction, heart failure, or stroke), percutaneous coronary intervention or coronary artery bypass grafting\*.
- Lung function (FEV1, FVC) post bronchodilator using spirometry performed to ATS/ERS standards (during the COVID-19 pandemic, lung function cannot be assessed safely and so this outcome will not be available on all participants).
- Breathlessness using Baseline and Transition Dyspnoea Indices (BDI & TDI).
- All-cause, respiratory and cardiac mortality\*.
- Serious adverse events, adverse reactions.
- Health related quality of life using EuroQoL 5D (EQ-5D-5L) Index.
- Disease specific health status using the COPD Assessment Test (CAT).
- Utilisation of primary or secondary health care for respiratory events\*.
- Change in disease associated symptoms using the Hull Airways Reflux Questionnaire (HARQ) [*this will only be done at some recruitment sites*].
- Modelled lifetime incremental cost per Quality Adjusted Life Year.

\*The time period will be the year of treatment, i.e. number events per year of treatment.

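### MACE is defined as a total number of events per year of treatment, but the chi-squared test fixed for it compares only how many participants had any event

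*Protocol*

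**What the plan says.** Protocol section 3.2 lists the total number of MACE among the secondary objectives, and the synopsis words the outcome the same way. Section 3.4 gives the endpoint as "Total number of major adverse cardiovascular events (MACE) (defined by cardiovascular death, hospitalisation for myocardial infarction, heart failure, or stroke", and adds percutaneous coronary intervention and coronary artery bypass grafting. The entry carries an asterisk, and the footnote reads: "The time period will be the year of treatment, i.e. number events per year of treatment".

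Section 10.3 gives the analysis in one sentence: "Major adverse cardiovascular events (MACE) in randomisation groups will be compared using the chi-squared test". It names no follow-up time, covariates or effect measure.

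The same section treats the two other endpoints worded as total numbers, COPD admissions and all-cause emergency admissions, differently. They "will each be analysed in the same way as for the primary outcome described above", that is, by "negative binomial regression with length of time in the study as an offset". In the text on that model, participants lost to follow-up, "estimated to be around 15% of those randomised", contribute data until they are lost. Deaths are put at around 6%.

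**The concern.** A chi-squared test on participants needs one any/none classification for each person. The quantity compared is therefore the proportion with at least one MACE, not a number of events or a rate. Three things follow.

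- A participant with a myocardial infarction admission and a later revascularisation counts once, although the endpoint counts both.
- A participant lost at three months with no known event must be either counted as event-free for the year or left out. Neither matches the rule for the sibling counts.
- The result does not estimate the quantity defined in 3.4, so the report will either present a test that does not belong to its endpoint or change the method after the fact.

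The SAP is not shown, but this is not a matter the protocol leaves to it: the protocol itself fixes the test.

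**Working it through.** **1. The plan's own figures.** The protocol states no MACE rate, difference or power. Its only sample size is for the primary outcome (section 10.1: SD 1.86, means 2.22 and 1.89, 90% power, two-sided 5%):

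n = 2 × (1.960 + 1.282)² × 1.86² / 0.33² ≈ 668 per arm, against 669 stated. 669 / 0.85 = 787.06, against 787 stated.

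These reproduce, and nothing below changes them, because the sample size does not rest on MACE.

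**2. Endpoint against method.**

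| Endpoint | Form in 3.4 | Method in 10.3 | Uses partial follow-up? |
|---|---|---|---|
| COPD admissions | total number, per year of treatment | negative binomial, time offset | yes |
| Emergency admissions | total number, per year of treatment | negative binomial, time offset | yes |
| All-cause mortality | per year of treatment (footnote) | log-rank, Cox | yes |
| MACE | total number, per year of treatment | chi-squared | no |

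**3. Repeat events lost by any/none coding.** Assumed inputs, since the protocol gives none: rate r of 0.02 to 0.10 per participant-year and negative binomial dispersion k of 0 to 3. With a full year of follow-up, P(any) = 1 − (1 + kr)^(−1/k), or 1 − exp(−r) when k = 0. The share of events lost is 1 − P(any)/r.

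| r | k = 0 | k = 1 | k = 3 |
|---|---|---|---|
| 0.02 | 1.0% | 2.0% | 3.8% |
| 0.05 | 2.5% | 4.8% | 9.0% |
| 0.10 | 4.8% | 9.1% | 16.3% |

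At r = 0.05 and k = 1 this is 4.8% of 1,574 × 0.05 ≈ 79 events, or about 4 events.

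**4. Equal dropout.** Simulation with 787 per arm, 15% in each arm leaving at a uniform time in the year, and 4,000 runs. An uncorrected chi-squared test on any MACE is compared with a person-time rate ratio with robust variance.

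| Assumed rate, true rate ratio, k | Rejections, chi-squared | Rejections, rate ratio |
|---|---|---|
| 0.05, 1.0, 1 | 5.6% | 5.0% |
| 0.05, 0.6, 1 | 45.2% | 46.0% |
| 0.10, 0.7, 1 | 43.3% | 46.5% |
| 0.10, 0.7, 3 | 37.4% | 41.8% |

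With no true effect the median chi-squared risk ratio is 1.00. The power lost is 0.8, 3.2 and 4.4 points.

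**5. Unequal dropout, no true effect.** If a share d leaves half-way on average, exposure is 1 − d/2.

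| Dropout by arm | Exposure ratio | Assumed rate | Median risk ratio, any MACE | Type I error, chi-squared | Type I error, rate ratio |
|---|---|---|---|---|---|
| 10% v 20% | 0.90/0.95 = 0.947 | 0.05 | 0.944 | 5.1% | 4.4% |
| 10% v 30% | 0.85/0.95 = 0.895 | 0.05 | 0.897 | 7.5% | 5.0% |
| 10% v 30% | 0.895 | 0.10 | 0.901 | 9.4% | 5.1% |

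The median person-time rate ratio stays between 0.996 and 1.002. The 10% v 20% split averages the protocol's 15%. The 10% v 30% split averages 20%, which fits only if the 6% deaths are added.

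**6. The shift against sampling error.** For 10% v 20%, ln(0.947) = −0.054. The standard error of the log risk ratio is √[2(1 − p)/(np)]. With n = 787 and an assumed p = 0.05, it is √(1.90/39.35) = 0.22, so the shift is about 0.25 of one standard error. At p = 0.02 the standard error is 0.35 (0.15 of it); at p = 0.10 it is 0.15 (0.36 of it).

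**The case against.** The footnote in 3.4 proves less than it seems to. It is also attached to mortality and to health care utilisation, and a death cannot recur, so it can be read as fixing the observation window rather than calling for a rate model. This stands. What remains is the wording total number, in the synopsis, 3.2 and 3.4, and that is enough: the same wording leads to an offset count model for the admissions.

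Section 10.3 also says "Poisson regression may be used to compare multiple events of the same type between randomisation groups". That sentence is optional, follows the text on utilisation and adverse events, and does not name MACE. The later sentence that does name MACE says chi-squared. It softens the gap without closing it.

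Follow-up will be better than the 15% loss figure suggests. Section 7.6 plans attempts to check GP records for MACE in those with no 12-month data, and section 7.10 asks people who stop treatment to stay in follow-up or allow use of their records. Cardiovascular deaths are themselves MACE, so part of the 6% is counted events. All of this stands and reduces the size of the problem.

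A reader might infer that the chi-squared test biases the MACE result towards one arm. The documents do not support that. The bias needs unequal follow-up, and the protocol predicts none. Section 8.7.1 cites similar intolerance on bisoprolol and placebo in heart failure studies. Appendix 8 reports no significant difference in dose reductions triggered by lung function (9% v 13%). Neither measures loss to follow-up, but neither points to a large imbalance.

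**Conclusion.** The mismatch is real and is fixed in the protocol: the endpoint is a number of events over time, while the test compares proportions of participants, without repeat events or person-time. It is a minor point. With balanced follow-up the two analyses nearly agree, and the cost is about 1 to 4 points of power. With moderately unequal dropout the shift is about a quarter of one standard error at a 5% risk. Type I error rises clearly only at the extreme 10% v 30% split. Every MACE rate, dispersion value and dropout split used here is an assumption.

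It would also go too far to call MACE the key outcome of the trial. It is one of a long list of secondary endpoints, the protocol does not rank it above the others, and it plays no part in the sample size.

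**What to change.** Replace the MACE sentence in 10.3. Analyse MACE as an event rate by Poisson regression with robust variance, or by negative binomial regression, with log follow-up time as offset. If events are few, analyse time to first MACE by log-rank test and Cox regression. Keep the chi-squared comparison as descriptive.

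Adjust only as far as the event count allows. At the assumed rates, 1,574 participants yield about 31 (× 0.02) to 157 (× 0.10) events, and the lay summary plans 160 centres. That is about one event per centre or fewer, so a full set of centre terms could be unstable.

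If the any/none form is what is wanted, reword the synopsis, 3.2 and 3.4 to participants with at least one MACE and use the time-to-first-event analysis.

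In either case, state whether follow-up means time in study (10.3) or the year of treatment (3.4). The two differ because section 7.10 lists myocardial infarction and some heart failure diagnoses among the reasons for ending treatment.

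The cost is a sentence or two, with no change to sample size or visits. For time to first event, confirm that MACE dates are held for everyone: the SAE form records onset dates, but section 9.2 ends SAE recording 28 days after study drug is stopped early.
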